### Primary Efficacy Analysis

This study has co-primary endpoints: *NIHSS tests score* and *ADL score.* For each of the co-primary endpoints we will compute Overall Proportion of Success:

The following hypotheses are specified and will be tested separately:

For *NIHSS tests score* proportion of improvement:

H_0_: p_1_< p _2_

H_1_: p _1_> p _2_

While p1= 0.25 and p2=0.04

For *ADL score* proportion of improvement:

H_0_: p_1_< p _2_

H_1_: p _1_> p _2_

While p1= 0.25 and p2=0.04

Each of these hypotheses will be tested by:

1. Constructing a one-sided, lower 95% confidence interval about the observed Overall Proportion of Success in the relevant cohort.
2. Examining whether the lower limit of the confidence interval is at or above the success criterion

Study success will be declared if the following is met:

1. Lower confidence limit of HBOT treatment success is at 0.25 or above

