**Sample Size Considerations**

Presentation of sample size is based on achieving 80% power overall to demonstrate that improvement rate in *NIHSS test score* is at least 0.25 and, separately, that improvement rate in *ADL test score* is at least 0.25. An improvement rate of at least 25% in the NIHSS test and ADL score in the treatment group (comparing to baseline, prior to HBOT treatment) would be an appropriate clinical target for HBOT treatment success and of sufficient interest to encourage further investigation of HBOT treatment for post stroke patients suffering chronic NIHSS deficiencies.

Sample size was based on the assumption that exposure to the NIHSS tests and ADL evaluation (at baseline) without any additional training might induce up to 4% score improvement in the second NIHSS test (following treatment). Assuming a true success rate of 25% a sample of N = 31 will provide 80% power to show that HBOT treatment induces at least 25% improvement on *NIHSS test score* and separately, on *ADL test score*. This is based on a power analysis using the normal approximation for the binomial, with one-sided Alpha=0.05.

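### The success rule sets the lower confidence limit against 0.25, which is also the assumed true rate, so the chance of success under the plan's own assumption is about 3% to 6% per endpoint, not 80%

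*Protocol*

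**What the plan says.** Three statements in the Protocol bear on this point.

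- **Sample Size Considerations** gives the planning assumption and the power: "Assuming a true success rate of 25% a sample of N = 31 will provide 80% power". The method is stated as "This is based on a power analysis using the normal approximation for the binomial, with one-sided Alpha=0.05". The aim is described as "80% power overall to demonstrate that improvement rate in *NIHSS test score* is at least 0.25", and the same is said of ADL. The section also allows for up to 4% improvement from repeat testing alone.
- **Primary Efficacy Analysis, hypotheses**: for NIHSS and ADL alike, the alternative is p1 > p2, "While p1= 0.25 and p2=0.04".
- **Primary Efficacy Analysis, decision rule**: the test consists of "Constructing a one-sided, lower 95% confidence interval about the observed Overall Proportion of Success in the relevant cohort", followed by "Examining whether the lower limit of the confidence interval is at or above the success criterion". The criterion is then given as a number: "Lower confidence limit of HBOT treatment success is at 0.25 or above".

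**The concern.** In a test based on a lower confidence limit, the limit must clear the null or reference value, and power is computed at a larger assumed true value. Here the hypotheses make 0.04 the reference and 0.25 the planning alternative, but the rule compares the limit with 0.25. The assumed truth and the bar are the same number, so a treatment that performs exactly as planned will nearly always miss the bar.

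This is the only success criterion in the protocol. If HBOT achieved 25% responders, the trial would be declared a failure on each endpoint about 94% to 97% of the time, although the protocol promises 80% power. The conflict also leaves two candidate thresholds, 0.04 and 0.25, open to choice after the data are known. That matters more in a trial whose Randomization section accepts that ADL was not blinded and that blinding of NIHSS could not be assured.

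**Working it through.** **Inputs** (all from Sample Size Considerations and Primary Efficacy Analysis): p1 = 0.25, p2 = 0.04, one-sided alpha 0.05 (z = 1.645), power 80% (z = 0.842), N = 31, one-sided 95% lower limit, threshold 0.25. The protocol does not name the interval type or say whether 31 is per arm or in total, so the alternatives are shown.

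**1. Reproducing N = 31.** Two proportions, normal approximation, unpooled variance:

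n per arm = (1.645 + 0.842)² × (0.25 × 0.75 + 0.04 × 0.96) / (0.25 − 0.04)² = 6.185 × 0.2259 / 0.0441 = 31.7.

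Power with 31 per arm: 0.21 / √(0.2259 / 31) − 1.645 = 2.460 − 1.645 = 0.815, and Φ(0.815) = 79.3%.

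This is the closest match. Other one-sided calculations against 0.04 fit less well: two-sample pooled variance gives 34 per arm (76.9% power with 31), two-sample arcsine 29.8 per arm, one-sample score 10.7 and one-sample Wald 26.3. So N = 31 with about 80% power is, in substance, 0.25 against 0.04 with 31 per arm.

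**2. The rule as written, n = 31.** Find the smallest number of responders whose lower limit is at least 0.25. Wald limit: p̂ − 1.645 × √(p̂(1 − p̂)/31).

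- 12/31: 0.387 − 0.144 = 0.243, which fails.
- 13/31: 0.419 − 0.146 = 0.274, which passes.

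| Limit | Just fails | Just passes | P(success) at true rate 0.25 |
|---|---|---|---|
| Wald | 12/31 (0.243) | 13/31 (0.274) | P(X ≥ 13) = 2.9% |
| Exact (Clopper-Pearson) | 12/31 (0.241) | 13/31 (0.269) | P(X ≥ 13) = 2.9% |
| Wilson | 11/31 (0.230) | 12/31 (0.258) | P(X ≥ 12) = 6.4% |

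The last column is the exact binomial tail with n = 31 and p = 0.25. Agresti-Coull behaves like Wilson, and the continuity-corrected Wald limit like Wald.

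**3. Pooling all treated patients.** If 31 is per arm and both arms' HBOT periods are combined (n = 62), Wald, exact and Wilson all need 22/62, with probability 4.3%. The continuity-corrected Wald limit needs 23/62, with 2.3%.

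**4. True rate needed for 80% power under the written rule, n = 31.** P(X ≥ 13) reaches 80% at p = 0.479, and P(X ≥ 12) at p = 0.447.

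**5. The same limit compared with 0.04, n = 31, true rate 0.25.** Wald needs 5/31 and has 91.7% power. Exact and Wilson need 4/31 and have 96.9%. The continuity-corrected Wald limit needs 6/31 and has 82.4%.

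**The case against.** The strongest defence is that 0.25 is a deliberate bar. Sample Size Considerations calls a rate of at least 25% a suitable clinical target, and a sponsor may require proof that the rate exceeds it. That reading is legitimate, so it cannot be assumed that the threshold is the slip and the planning value is right. But power must then be computed at a true rate above 0.25, and the protocol computes it at exactly 0.25. The contradiction remains; only the choice of remedy is affected.

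The 0.25 and 0.04 are also used loosely. In places they read as the size of a score change, not as a proportion of patients. The binomial basis and the reference to a proportion of success support the responder reading used here, but it is an assumption.

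Some stronger readings are tempting and not supported:

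- **That the chance of success can never exceed 5%.** The nominal rate is about 5%, but the interval is not named, and a Wilson limit with n = 31 gives 6.4%. The normal approximation is specified for the power analysis, not for the interval.
- **That N = 31 is a miscalculation.** It agrees closely with 0.25 against 0.04 with 31 per arm.
- **That writing p1 and p2 as fixed numbers makes the null hypothesis false by definition.** The line reads naturally as planning values.
- **That replacing 0.25 with 0.04 restores the 80% figure.** A one-sample rule against 0.04 has about 92% to 97% power with the usual intervals.

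The possible existence of a separate analysis plan does not answer the point, because the protocol itself states the hypotheses, the power and the criterion, and they conflict.

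**Conclusion.** The point holds. The stated power and the decision threshold cannot both stand. At the plan's own true rate of 0.25, the chance of meeting the criterion with n = 31 is about 3% to 6% per endpoint, depending on the interval, and about 4% with 62 pooled patients. If NIHSS and ADL must both succeed, the joint chance is no higher. A larger sample does not help while the truth equals the bar.

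These figures assume that 0.25 and 0.04 are responder proportions; the pooled figure also assumes 31 per arm. The fault lies in the success rule and in the sentence claiming power to show at least 25%, not in the arithmetic behind N. The documents do not show whether the intended bar was 0.04, no difference between arms, or 0.25.

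**What to change.** Make the success rule, the hypotheses and the sample-size basis agree.

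- **Preferred.** Declare success on an endpoint when the one-sided 95% lower limit for the difference in success proportions (HBOT minus control) at 2 months exceeds 0. Keep 0.25 and 0.04 as planning values. In Sample Size Considerations, state about 79% to 80% power for 0.25 versus 0.04 with 31 per arm, and name the method.
- **If a one-sample rule against 0.04 is kept.** State its power as about 92% to 97% with n = 31 (Wald, or exact/Wilson), not 80%. Name the interval, and note that 4 or 5 responders of 31 (13% or 16%) would then count as success, well below the 25% target.
- **If 0.25 is meant as the bar to exceed.** Remove the 80% claim at a true rate of 0.25, and state that n = 31 gives 80% power only at a true rate of about 0.45 to 0.48.

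**Cost.** Each option is more than an edit of wording. The first two change the primary success criterion, and the first also brings the control arm into a rule that now uses none of its results. The change must be a formal amendment made before outcome data are seen. It needs no new procedures and, if 31 is per arm, no added patients. If 31 was meant as the total, the two-arm comparison would have only about 51% power (15.5 per arm, pooled-variance approximation), so the amendment must also say which is meant.

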**Randomization**

Since the diversity of the patients included in the study, after signing the informed consent was expected to be high, no stratifies criteria was used. Patients were randomized in 1:1 fashion to either treatment or controlled-cross group.

There is no placebo in the cross group during the control period. The only way to give “placebo” of HBOT, is to bring the patients to the hyperbaric chamber and to increase the environmental pressure- in a way the patients will “feel the hyperbaric pressure” in their ears. However, Henry’s law states: “the amount of a given gas dissolved in a given type and volume of liquid is directly proportional to the pressure of that gas in equilibrium with that liquid”. Thus, hyperbaric environment significantly increases the dissolved oxygen pressure even if a person holding his breath[^76^](#_ENREF_76). Moreover, the alternative of hosting the patients in the hyperbaric chamber without any pressure increase cannot serve as a real placebo since the patients will not feel the pressure. Accordingly, the only real “placebo” could be archived by increasing the pressure and reducing the percentages of the oxygen but that holds significant safety consideration.

From the ethical point of view, it was deemed unethical to “treat” the patients (40 sessions in the hyperbaric chamber) while they actually know that it is a placebo. In order to somewhat compensate for this limitation, the control was a cross group and after the 2^nd^ evaluation at the end of a control period they were crossed to HBOT. The cross for treatment enables intra-group efficacy evaluation in both treatment and control group.

Since the patients knew they were not receiving HBOT during the control period they were not blinded with regard to the treatment arm. Accordingly the ADL and quality of life evaluations were not blinded. Moreover, in the current clinical setting, it was not possible to assure that the NIHSS evaluation could be done completely blinded by the physician. The complete blindness evaluation could be assured in the brain SPECT evaluation done by the radiologist. The correlation between metabolic blinded evaluation of the brain (SPECT) and the neurological un-blinded evaluations give further support and strength to the clinical findings.

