**Inclusion criteria**

- Ischemic or hemorrhagic stroke 6-36 months prior to the inclusion in the study.
- All patients had to have persistent (stable non improving) neurologic deficiency that includes at least one motor dysfunction (paresis or plegia) without noticeable improvement during the last month prior to their enrolment.
- age 18 years or older

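### Expected patient diversity is given as the reason not to stratify, and the fixed primary analysis then makes no baseline adjustment in a small trial

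*Protocol*

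**What the plan says.** The Randomization section of the protocol explains the absence of strata by the expected mix of patients, which "was expected to be high, no stratifies criteria was used". Allocation is described only as "Patients were randomized in 1:1 fashion to either treatment or controlled-cross group"; no blocking, minimisation or other balancing is mentioned.

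The eligibility criteria bear out the expected diversity: "Ischemic or hemorrhagic stroke 6-36 months prior to the inclusion in the study", at age 18 or over, with a stable motor deficit but no limit on overall severity.

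The Primary Efficacy Analysis section fixes the method: "For each of the co-primary endpoints we will compute Overall Proportion of Success", followed by "Constructing a one-sided, lower 95% confidence interval about the observed Overall Proportion of Success in the relevant cohort". The lower limit is compared with 0.25. The section names no covariate, stratum or between-arm model. Baseline NIHSS and ADL are nevertheless collected on every patient.

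On size, the Sample Size Considerations section says that "a sample of N = 31 will provide 80% power", without stating whether that is per arm or in total.

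**The concern.** Diverse prognosis makes chance differences between small randomised groups matter more. That argues for balancing on a key factor, adjusting for it in the analysis, or both. Here diversity is offered as the reason for doing neither at allocation, and nothing later in the plan makes up for it.

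What is at stake is the comparison of two months of HBOT with two months of control. If one arm starts more severely affected by chance, part of any difference in improvement reflects where patients started. Precision that the baseline scores could supply at no cost also goes unused.

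**Working it through.** **Inputs.** From Sample Size Considerations: N = 31, 80% power, "normal approximation for the binomial, with one-sided Alpha=0.05". From Primary Efficacy Analysis: "While p1= 0.25 and p2=0.04". The baseline to month-2 correlation r is not in the protocol; 0.7 and 0.8 are assumed, with equal variances at the two times.

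**1. How large is the trial?** Two-sample normal approximation with unpooled variance:

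n per arm = (1.645 + 0.842)² × (0.25 × 0.75 + 0.04 × 0.96) / (0.25 − 0.04)² = 6.18 × 0.2259 / 0.0441 = 31.7, so 32.

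At 31 per arm this formula gives 79.3% power. Other one-sided versions give 34 per arm (pooled variance) or 30 (arcsine). One-sample versions give 11 (null variance) or 27 (alternative variance). The stated 31 therefore fits best as a per-arm figure, about 62 patients in all. If 31 is the total, power for the two-sample comparison is about 51% (pooled). Both sizes are carried forward.

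**2. Chance of baseline imbalance.** For a continuous factor, P(|difference| > d SD) = 2[1 − Φ(d / √(1/n₁ + 1/n₂))].

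| Size | Standard error (SD units) | 0.3 / SE | P(> 0.3 SD) |
|---|---|---|---|
| 31 per arm | √(2/31) = 0.254 | 1.18 | 24% |
| 31 in total (15 and 16) | √(1/15 + 1/16) = 0.359 | 0.83 | 40% |

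For a two-level factor such as stroke type, with an assumed prevalence of 30 to 50%, the chance that the arms differ by 10 percentage points or more is 33 to 37% with 62 patients and 56 to 58% with 31.

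**3. Effect on a between-arm comparison of improvement.** The planned outcome is improvement from the patient's own baseline, so the nearest simple comparator is the change score. With equal variances, a baseline imbalance of d shifts the difference in mean change by (1 − r)d in absolute terms. The worse-starting arm appears to improve more. The variance of change is 2(1 − r); after adjustment for baseline it is 1 − r² (both in units of the score variance).

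| r | Shift at d = 0.3 SD | Variance, change | Variance, ANCOVA | Reduction |
|---|---|---|---|---|
| 0.8 | 0.2 × 0.3 = 0.06 SD | 0.40 | 0.36 | 10% |
| 0.7 | 0.3 × 0.3 = 0.09 SD | 0.60 | 0.51 | 15% |

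For scale, with 31 per arm the standard error of the difference in mean change is √0.40 × 0.254 = 0.161 SD at r = 0.8 and √0.60 × 0.254 = 0.197 SD at r = 0.7. The shift is thus 0.06/0.161 = 0.37 or 0.09/0.197 = 0.46 of a standard error.

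**4. What this does not cover.** The planned endpoint is a success proportion, not a mean change, and step 3 does not model that. Dichotomising does not remove the dependence on baseline. If success is read as a 25% improvement per patient on the ADL scale (0 to 51), a patient starting at 4 needs one point and a patient starting at 40 needs ten.

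**The case against.** The strongest reply has four parts.

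- **Unstratified randomisation is a recognised choice.** This is correct. It is valid and unbiased in expectation, and with many candidate factors and few patients it can be sensible not to stratify. But the sentence does not give that reason, and that reason would itself point towards adjustment in the analysis.
- **The written test cannot be distorted by imbalance between arms.** This also stands. A reader might infer that imbalance undermines the declared success rule. It does not, because that rule sets one cohort's lower limit against a fixed 0.25 and compares no arms. The exposure lies in the comparison implied by 1:1 allocation to a control period and by p1 versus p2, where the 4% is the improvement expected from retesting alone. That no between-arm test is specified is a separate and larger matter.
- **Baseline is already used, and the crossover gives within-patient contrasts.** This is largely right, and it limits the size of the effect. A reader might compare adjustment with unadjusted month-2 scores and obtain a shift of 0.8 × 0.3 = 0.24 SD and a variance cut of 0.8² = 64% at r = 0.8. The protocol plans no such analysis, so those figures do not describe it. The before-and-after contrasts within the cross group are untouched by imbalance, but they are not a randomised comparison.
- **Stratifying on baseline NIHSS is impractical.** A reader might infer that strata should now be added. The Study protocol section places the baseline evaluation after randomisation, and its past tense suggests that allocation may be complete. The documents do not support that remedy.

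**Conclusion.** The point holds in a limited form. The stated rationale is wrong, and the fixed primary analysis adjusts for nothing although the baseline scores are available. The consequence is a 24 to 40% chance of a baseline difference above 0.3 SD, depending on how N = 31 is read. Against simple change scores, such a difference would shift the between-arm result by about 0.06 to 0.09 SD, and adjustment would also reduce variance by about 10 to 15%. This is a modest, conditional effect, not a bias in expectation or a flaw in the validity of the randomisation.

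The imbalance probabilities rest on a normal approximation and full arm sizes; losses from the completer analysis set would raise them slightly. The shift and variance figures rest on r = 0.7 to 0.8 and equal variances, neither of which the protocol supplies, and they apply to mean scores, not to the success proportion.

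**What to change.** 1. In the Randomization section, delete the clause that gives expected diversity as the reason for not stratifying. State simply that allocation was 1:1 without stratification.
2. In the Primary Efficacy Analysis section, specify a between-arm comparison of month-2 NIHSS and month-2 ADL (after HBOT in the treated group, after the control period in the cross group) by ANCOVA, adjusted for the patient's own baseline value of the same score. Stroke type may be named in advance as a second covariate, but it is optional.

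No change to allocation is proposed. The cost is one or two lines of analysis text; the scores are already collected at both times, so there are no new data and no added burden on patients.

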***Study protocol***

After signing the informed consent, patients were randomized in 1:1 manner into the treated or the control-cross group. After the randomization, patients were invited for baseline evaluation that included full review of their medical status and complete physical examination. All patients had baseline CT scan. After their inclusion patients were randomized to two groups: a treated group and a cross group. All patients had evaluation of their neurologic functions by physical examination, ability to perform activities of daily living, quality of life and brain functional imaging (rCBF-SPECT scan). The patients in the treated group were evaluated twice – at baseline and after 2 months of HBOT treatment. The patients of the cross group were evaluated three times – at baseline, after a 2 month control period of no treatment and after a consequent 2 month period of HBOT treatment. We emphasize that the study was a cross-over trial and patients in the cross group received HBOT treatment after their second evaluation and had a third neurological evaluation after the cross, when they have completed their HBOT.

The following HBOT treatment protocol was practice: The patient were treated 40 times (each treatment session was given on a separate day) distributed over two months (five days a week). Each session was for 90 minutes in 100% oxygen atmosphere and at pressure of 2 ATA.

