**Brain functional Imaging SPECT imaging and Analysis**

Single photon emission computed tomography (SPECT) will be conducted before and after HBOT. Subjects will lay supine in a quiet dimly lit room for 20 min prior to injection of the radiopharmaceutical. Apart from administration of the injection by a physician, they will remainalone in the room during this period. Subjects will be asked to remain at rest for 10 min after the injection of the radiopharmaceutical to allow uptake of the radiopharmaceutical in the brain.

An injection of 925-1110 MBq (25-30 mCi) of technetium-99m ethyl cysteinate dimmer (Tc-99m-ECD) will be given into an arm vein through a previously placed intravenous cannula. SPECT imaging of the brain was performed, at 40-60 min post injection, with the subject’s head supported by a headrest, using a dual detector gamma camera (ECAM or Symbia T, Siemens Medical Systems) equipped with high resolution collimators. Data will be acquired in the step-and-shoot mode, using a 360 degree circular orbit, with the detectors of the gamma camera as close as possible to the subject’s head. The camera used for imaging will noted for each subject and the same camera will be used for the follow-up study. Data will be acquired using a 128׳128 image matrix in 3 degree steps of 20 seconds per step. Data will be reconstructed by iterative reconstruction with no filtering. The Chang method (*μ*=0.12/ cm) will be used for attenuation correction.

Intra subject visual analysis will be conducted using a process in which pre and post treatment studies are fused and normalized to pre-treatment whole brain activity.

Visual analysis will be carried out by two nuclear medicine physicians who compared the scans independently and grad them as either: 1=no change, 2=mild change and 3=significant change. Where, no change is assign when no visual difference is noted in the number or size of perfusion deficits, mild change is given when a reduced number of perfusion defects are noted or the size of the perfusion defects is reduced. Significant change should be attributed when a global perfusion increment is observe in addition to diminution of defect numbers or size. Differences in evaluation will be resolve after reviewing the images together. Scan visual interpretation will be carried out while blinded to any laboratory or clinical data.

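### The protocol says correlation with blinded SPECT strengthens the unblinded NIHSS and ADL results, but if treated and untreated observations are combined, a SPECT effect plus rating bias can produce that correlation without clinical benefit

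*Protocol*

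**What the plan says.** The Randomization section of the protocol is candid about blinding. Patients know their arm, and the control condition has no sham: "There is no placebo in the cross group during the control period". On the patient-reported outcomes: "Accordingly the ADL and quality of life evaluations were not blinded". On the stroke scale: "it was not possible to assure that the NIHSS evaluation could be done completely blinded by the physician". Only the scan reading is described as fully blinded, and the imaging section agrees: "Scan visual interpretation will be carried out while blinded to any laboratory or clinical data".

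The Randomization section then closes with an unconditional statement: "The correlation between metabolic blinded evaluation of the brain (SPECT) and the neurological un-blinded evaluations give further support and strength to the clinical findings".

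NIHSS and ADL are the co-primary endpoints under Primary Efficacy Analysis. SPECT is also listed among the primary endpoints under Objectives. The SPECT result is an ordinal change grade, "1=no change, 2=mild change and 3=significant change". Under Study protocol, SPECT and the clinical scales are collected in both groups: "All patients had evaluation of their neurologic functions by physical examination, ability to perform activities of daily living, quality of life and brain functional imaging". The protocol does not say whether the correlation is taken across arms, within an arm, within a period, or with adjustment for treatment.

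**The concern.** Blinding one of two correlated measures does nothing to the bias in the other. Two measures that both differ by exposure will correlate when exposed and unexposed observations are combined, even if they are unrelated among patients with the same exposure.

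Two ingredients are needed, and the protocol leaves room for both. The first is a SPECT change with HBOT, which the Background leads the reader to expect, since it cites improved cerebral blood flow on SPECT in chronic neurological deficiency. The second is favourable scoring of treated patients, which is possible with an untreated comparator and raters and patients who may know the arm.

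In that setting the correlation cannot tell a real neurological gain from generous rating, yet the protocol has already said what it will mean. A positive result could then be presented as blinded corroboration of NIHSS and ADL.

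**Working it through.** **Inputs from the protocol.** Allocation is 1:1 (Randomization). The SPECT grade has three levels (imaging section). Sample Size Considerations gives N = 31, 80% power, one-sided alpha 0.05 and rates of 0.25 and 0.04, without saying whether 31 is per arm or in total.

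**Reading of N = 31.** As a per-arm two-proportion size with unpooled variance:

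n = (1.645 + 0.842)² × (0.25×0.75 + 0.04×0.96) / 0.21² = 6.18 × 0.2259 / 0.0441 ≈ 31.7, rounded up to 32.

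The arcsine version gives 30 and the pooled-variance version 34. A per-arm reading is therefore plausible but not stated. Below, 31 per arm is an assumption, and the argument does not depend on it.

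**Inputs not in the protocol (assumed, shown as a range).** d is the SPECT shift with treatment and b the rating bias in favour of treated patients, both in within-arm SD. ρ is the within-arm correlation, set to 0. There is no true clinical effect.

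**Closed form for two equal arms combined.**

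r = (ρ + d·b/4) / √[(1 + d²/4)(1 + b²/4)]

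- d = 0, any b: r = 0
- d = 0.5, b = 0.5: 0.0625 / 1.0625 = 0.06
- d = 1, b = 0.5: 0.125 / √(1.25 × 1.0625) = 0.11
- d = 1, b = 1: 0.25 / 1.25 = 0.20
- d = 1.5, b = 1.5: 0.5625 / 1.5625 = 0.36
- d = 2, b = 2: 1 / 2 = 0.50

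The numerator is a product, so both shifts are required.

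**Simulation on the protocol's own type of scale.** Three-level SPECT grade, continuous clinical change, Spearman correlation, two-sided 5% test, 31 per arm, 3,000 trials per setting. Assumed control grades (levels 1/2/3) are 70/20/10%. Assumed treated grades are the same for no shift, 40/35/25% for a moderate shift and 20/35/45% for a large shift.

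| SPECT shift | Bias (SD) | Mean combined r | Combined test significant |
|---|---|---|---|
| None | 0.5 / 1 / 1.5 | about 0 | 5.7% / 6.1% / 4.6% |
| Moderate | 0.5 / 1 / 1.5 | 0.07 / 0.14 / 0.19 | 9.0% / 20.2% / 30.9% |
| Large | 0.5 / 1 / 1.5 | 0.13 / 0.23 / 0.325 | 17.1% / 45.5% / 74.2% |

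Within the treated arm alone, mean r was about 0 and the test was significant in 4.5% to 5.6% of trials in every setting. The Monte Carlo standard error at 5% is √(0.05 × 0.95 / 3000) ≈ 0.4 percentage points, so these rates are consistent with the nominal level.

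**Limit of the within-arm result.** It assumes the bias is the same for every treated patient. The protocol keeps scan readers unaware of clinical data, but nowhere keeps NIHSS raters or patients unaware of the scan. If they learn the result and score accordingly, bias follows the scan patient by patient and a within-arm correlation appears as well.

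**The case against.** The strongest reply is that the protocol never says the data will be combined across exposure. The imaging section describes scans before and after HBOT, compared within each subject, and the Randomization section stresses within-group evaluation: "The cross for treatment enables intra-group efficacy evaluation in both treatment and control group". On that reading a uniform rating bias causes no artefact, and the method for a supportive correlation may properly be left to an analysis plan that is not at hand. This stands in part. A combined analysis is left open, not prescribed, and the missing method is not itself the fault. What remains is that the protocol settles the interpretation in advance and without condition, although an analysis it permits cannot support it.

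Four stronger readings are tempting, and the documents support none of them:

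- **Rating bias alone creates the correlation.** It does not. Without a SPECT shift the combined correlation is zero.
- **The correlation is offered as the remedy for missing blinding.** The text claims only added support. What it presents as partial compensation is the cross-over, and that is for the absent placebo.
- **Study success could be declared falsely.** Primary Efficacy Analysis rests on confidence limits for success proportions, and the correlation enters no hypothesis, success criterion or sample-size calculation.
- **The correlation is uninformative however it is computed.** A within-exposure association would carry some information, subject to the limit on knowledge of the scan.

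It is also fair to object that the size of the artefact rests on assumed shifts. It does, which is why a range that includes zero is shown.

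**Conclusion.** The point holds in conditional form. The protocol's unconditional claim does not follow: over treated and untreated observations together, a SPECT effect of HBOT plus favourable open-label rating suffices to produce the correlation with no clinical benefit. Under the assumptions stated, false support arises in about 9% to 31% of trials with a moderate SPECT shift and 17% to 74% with a large one, against roughly the nominal 5% when there is no SPECT shift or when only treated patients are analysed.

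These rates depend on the assumed grade distributions, a rating bias of 0.5 to 1.5 SD, no within-arm association and 31 per arm. The direction of the artefact does not depend on the particular values, provided both shifts favour treatment. The consequence is over-interpretation of the two co-primary results, with no effect on the formal success decision.

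**What to change.** - Compute any SPECT-clinical association within exposure group (treated arm, control period) or adjusted for treatment, and label it exploratory.
- Present the blinded between-arm SPECT comparison on its own, as evidence about perfusion.
- Replace the closing sentence of the Randomization section with one saying that the association does not offset the open-label rating of NIHSS, ADL and EQ-5D.
- State whether NIHSS raters and patients could learn the scan result before the clinical assessment. Within-group analysis removes only bias that is uniform within the group, so this limitation should be reported with the result.

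The cost is a few sentences and a within-group or adjusted correlation, with no new data or patients. The downside is a less favourable supporting claim.
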